## Methods of measurements

The same method of assessment and the same technique should be used to characterize each identified and reported lesion at baseline and during follow-up. Assessments should be identified on a calendar schedule and should not be affected by delays in therapy, which may be treatment arm dependent. While on study, all target lesions recorded at baseline should have their actual measurements recorded on the CRF at each subsequent evaluation, even when very small (e.g. 2 mm). If it is the opinion of the radiologist that the lesion has likely disappeared, the measurement should be recorded as 0 mm. If the lesion is believed to be present and is faintly seen but too small to measure, a default value of 5 mm should be assigned. For lesions which fragment/split add together the longest diameters of the fragmented portions; for lesions which coalesce, measure the maximal longest diameter for the “merged lesion”.

- **Clinical Lesions.** Clinical lesions will only be considered measurable when they are superficial and  $\geq 10$  mm as assessed using calipers (e.g. skin nodules). For the case of skin lesions, documentation by colour photography including a ruler to estimate the size of the lesion is recommended. If feasible, imaging is preferred.
- **Chest X-ray.** Chest CT is preferred over chest X-ray, particularly when progression is an important endpoint, since CT is more sensitive than X-ray, particularly in identifying new lesions. However, lesions  $\geq 20$  mm on chest X-ray may be considered measurable if they are clearly defined and surrounded by aerated lung.
- **CT, MRI.** CT is the best currently available and reproducible method to measure lesions selected for response assessment. This guideline has defined measurability of lesions on CT scan based on the assumption that CT slice thickness is 5 mm or less. When CT scans have slice thickness greater than 5 mm, the minimum size for a measurable lesion should be twice the slice thickness. MRI is also acceptable in certain situations (e.g. for body scans). While PET scans are not considered adequate to measure lesions, PET-CT scans may be used providing that the measures are obtained from the CT scan and the CT scan is of identical diagnostic quality to a diagnostic CT (with IV and oral contrast).
- **Ultrasound.** Ultrasound is not useful in assessment of lesion size and should not be used as a method of measurement. If new lesions are identified by ultrasound in the course of the study, confirmation by CT should be obtained.
- **Endoscopy, Laparoscopy.** The utilization of these techniques for objective tumor evaluation is not advised. However, they can be useful to confirm complete pathological response when biopsies are obtained or to determine relapse in trials where recurrence following complete response or surgical resection is an endpoint.
- **Tumor Markers.** Tumor markers alone cannot be used to assess objective tumor response. If markers are initially above the upper normal limit, however, they must normalize for a patient to be considered in complete response.
- **Cytology, Histology.** These techniques can be used to differentiate between PR and CR in rare cases if required by protocol (for example, residual lesions in tumor types such as germ cell tumors, where known residual benign tumors can remain). When effusions are known

to be a potential adverse effect of treatment (e.g. with certain taxane compounds or angiogenesis inhibitors), the cytological confirmation of the neoplastic origin of any effusion that appears or worsens during treatment when the measurable tumor has met criteria for response or stable disease is advised to differentiate between response or stable disease and progressive disease.

### 8.3.2 Tumor response evaluation

All patients will have their BEST RESPONSE from the start of atezolizumab until the end of treatment classified as outlined below:

**Complete or partial responses may be claimed only if the criteria for each are met at a subsequent time point at least 6 weeks later (table 2).**

Complete Response (CR): disappearance of all *target* and *non-target* lesions and normalization of tumor markers. Pathological lymph nodes must have short axis measures < 10 mm (Note: continue to record the measurement even if < 10 mm and considered CR). Tumor markers must have normalized. Residual lesions (other than nodes < 10 mm) thought to be non-malignant should be further investigated (by cytology or PET scans) before CR can be accepted.

Partial Response (PR): at least a 30% decrease in the sum of measures (longest diameter for tumor lesions and short axis measure for nodes) of target lesions, taking as reference the baseline sum of diameters. Non target lesions must be non-PD.

Stable Disease (SD): Neither sufficient shrinkage to qualify for PR nor sufficient increase to qualify for PD taking as reference the smallest sum of diameters on study.

Progressive Disease (PD): at least a 20% increase in the sum of diameters of measured lesions taking as references the smallest sum of diameters recorded on study (including baseline) AND an absolute increase of  $\geq 5$  mm. Appearance of new lesions will also constitute PD (including lesions in previously unassessed areas). In exceptional circumstances, unequivocal progression of non-target disease may be accepted as evidence of disease progression, where the overall tumor burden has increased sufficiently to merit discontinuation of treatment, for example where the tumor burden appears to have increased by at least 73% in volume (which is the increase in volume when all dimensions of a single lesion increase by 20%). Modest increases in the size of one or more non-target lesions are NOT considered unequivocal progression. If the evidence of PD is equivocal (target or non-target), treatment may continue until the next assessment, but on further documentation, the earlier date must be used.

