### 3.4 Endpoints

The primary endpoint is:

Proportion of patients who remain free of progression at 6 months. Progression as defined by RECIST 1.1 [34] will be used.

The secondary endpoints are:

- Proportion of patients free of progression (RECIST 1.1[34]) at 6 months in the IR-profile subgroup vs the non-IR-subgroup as defined by gene expression profiling(retrospectively defined as previously described [9])
- Proportion of patients who remain free of progression at 12 months. Progression as defined by RECIST 1.1 [34] will be used.
- Progression as defined by iRECIST [17]
- Overall survival

- Percentage of patients with toxicity (according to CTCAE v4.03, Appendix A) and immune-related toxicity defined as the Adverse Events of Special Interest (AESI's) for atezolizumab (see section 6 and Investigator's Brochure for atezolizumab)
- Objective response rate (RECIST 1.1[34])

*The exploratory endpoints are listed in Section 10 Translational Research*

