**Every 6 weeks, every 9 weeks after 6 months:**

- ◆ Tumor measurements by CT scan thorax/abdomen (**official response evaluation**). Measurements should continue until progression, also in case patient is taken off study for another reason.

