### **7.4 Ongoing response or stable disease at 12 months (18 cycles)**

Atezolizumab will be given until tumor progression or intolerable toxicity. After 12 months of atezolizumab treatment discontinuation is allowed in case of ongoing response or stable disease. At signs of progression after discontinuation of the treatment, atezolizumab can be re-started. The follow-up in this treatment-free period should be done as follow:

- ◆ Every four weeks: symptom directed physical exam, collect information on adverse events.  
Laboratory testing: hematology (Hb, leukocytes and differentiation, platelets), biochemistry (glucose, creat, urea, sodium, potassium, magnesium, chloride, calcium, phosphate, albumin, bilirubin, γGT, AF, AST, ALT, LDH, CRP, TSH, free T4, CEA, CA15.3.
- ◆ Every eight weeks: CT-scan (after 6 months: every 12 weeks).

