### 8.2 Modified RECIST 1.1 for immune-based therapeutics (iRECIST)

In rare occasions during first evaluation (after 4 cycles) of response to atezolizumab imaging may show small new lesions in the presence of other responsive lesions. In these cases, response evaluation according to iRECIST requires confirmation of progression by a repeat, consecutive assessment no less than 4 weeks from the date first documented, while RECIST 1.1 will define this as PD. If no further progression is seen on the confirmation scan, treatment will be continued according to protocol and imaging will be performed according to the original schedule.

Accumulating evidence indicates a minority of subjects treated with immunotherapy may derive clinical benefit despite initial evidence of PD.[16] At ASCO 2014 it has been presented that conventional criteria such as RECIST [34] may underestimate the benefit of anti-PD1 in approximately 10% of treated melanoma patients. [44] In this view, subjects will be permitted to continue atezolizumab treatment beyond initial RECIST 1.1 defined PD as long as they meet the following criteria (according to iRECIST):

- ◆ Investigator-assessed clinical benefit
- ◆ The possible progression seen on imaging is not putting the patient at risk for tumor-related complications
- ◆ Subject is tolerating study drug

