The assessment of clinical benefit should take into account whether the subject is clinically deteriorating and unlikely to receive further benefit from continued treatment. All decisions to continue treatment beyond initial progression must be discussed with the investigator and documented in the study records. Subjects should discontinue study therapy upon further evidence of further progression, defined as an additional 10% or greater increase in tumor burden volume from time of initial progression (including all target lesions and new measurable lesions). New lesions are considered measurable at the time of initial progression if the longest diameter is at least 10 mm (except for pathological lymph nodes, which must have a short axis of at least 15 mm). Any new lesion considered non-measurable at the time of initial progression may become measurable and therefore included in the tumor burden measurement if the longest diameter increases to at least 10 mm (except for pathological lymph nodes, which must have an increase in short axis to at least 15 mm). For statistical analyses that include the investigator-assessed progression date, subjects who continue treatment beyond initial investigator-assessed, RECIST 1.1-defined progression will be considered to have investigator-assessed progressive disease at the time of the initial progression event (according to iRECIST).

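### The RECIST 1.1 best-response window in section 8.3.2 ends with treatment rather than at first progression, so the secondary ORR can include post-progression responses and is unclear about off-treatment scans

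*Protocol*

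**What the plan says.** - **Endpoint.** Section 3.4 lists objective response rate by RECIST 1.1 as a secondary endpoint and iRECIST progression as a separate one. Section 9.5 reports ORR in the per protocol population with 85% and 95% confidence intervals.
- **Window.** Section 8.3.2: "All patients will have their BEST RESPONSE from the start of atezolizumab until the end of treatment classified as outlined below".
- **Confirmation.** Section 8.3.2: "Complete or partial responses may be claimed only if the criteria for each are met at a subsequent time point at least 6 weeks later".
- **Treatment past progression.** Section 8.2: "subjects will be permitted to continue atezolizumab treatment beyond initial RECIST 1.1 defined PD as long as they meet the following criteria". Sections 6.1.5 and 8.1 say the same in substance. Where a confirmation scan shows no further progression, section 8.2 adds that "treatment will be continued according to protocol and imaging will be performed according to the original schedule".
- **Restart.** Section 7.4, like sections 4.1 and 6.1.5: "At signs of progression after discontinuation of the treatment, atezolizumab can be re-started".
- **Date of progression.** Section 8.2 places progression at the initial RECIST 1.1 event, but opens that rule with "For statistical analyses that include the investigator-assessed progression date".
- **Scans after stopping for another reason.** Section 7.2.6: "Measurements should continue until progression, also in case patient is taken off study for another reason". Section 7.4 also keeps CT scans going in the treatment-free period after 12 months.

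**The concern.** A window bounded by treatment does little harm when treatment always stops at progression. In this trial it need not, and scans can also outlast treatment. The window and the RECIST 1.1 course of the disease can therefore separate in both directions.

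If the window runs past progression, shrinkage that belongs under iRECIST can enter an endpoint labelled RECIST 1.1. One patient can then fail the primary endpoint and still be counted as a responder on the same criteria. If the window closes before scanning ends, the protocol requires response scans and does not say whether they count. Either way, two analysts following section 8.3.2 could report different ORRs from the same data, and comparison with RECIST 1.1 rates elsewhere is weakened.

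**Working it through.** **1. The plan's own figures.** The protocol states no target or sample size for ORR, so there is no ORR figure to reproduce. The two-stage design for the primary endpoint (section 9.2: 22 then 18 patients, stop at 2 or fewer, reject at 8 or more of 40) was checked as the sum over x = 3 to 22 of P(X1 = x) × P(X2 ≥ 8 − x). This gives 0.0398 at a true proportion of 10% and 0.803 at 25%, against the stated 0.04 and 80%. It uses freedom from progression only. Best response does not enter it.

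**2. Can a response after progression count?** Take a baseline sum of 100 mm purely for illustration.
- Progression needs a 20% rise over the smallest sum and at least 5 mm: 100 × 1.20 = 120 mm, a rise of 20 mm. This is RECIST 1.1 PD.
- Partial response needs a 30% fall from baseline: 100 × 0.70 = 70 mm or less.
- Calendar with carboplatin day 1 as week 0: atezolizumab cycles fall at weeks 2, 5, 8 and 11, so the evaluation after 4 cycles (section 8.1) is at about week 14. Six-weekly CTs then fall at weeks 20 and 26.
- Suppose the sum is 120 mm at week 14, atezolizumab continues under section 8.2, and the sum is 70 mm at weeks 20 and 26. The patient progressed before 24 weeks, so the primary endpoint is a failure. Weeks 20 and 26 lie within the treatment window and are 6 weeks apart, so the confirmation rule is met.
- Table 3 in section 8.3.2 has no row with PD as the first time point, so it does not exclude this sequence. The section 8.2 rule on the date of progression does not reach ORR, which uses no date.

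**3. New lesions.** Table 2 in section 8.3.2 gives PD whenever a new lesion is present, and PR or CR only when there is none. Progression by new lesion therefore leads to a later response only if that lesion resolves.

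**4. Scans after treatment stops.** Suppose, for illustration, that treatment stops for toxicity at week 17.
- PR first seen at week 20: the scan is required by section 7.2.6, but it falls after the end of treatment and so outside the window.
- PR at week 14 and again at week 20: the confirmation sentence asks for a later time point and does not say it must be on treatment. If week 20 is accepted, Table 3 gives PR then PR, which is PR. If it is set aside as outside the window and treated as not evaluable, PR then NE becomes SD or NE. The text does not settle which applies.

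**5. End of treatment.** Because atezolizumab may be restarted after a treatment-free period, this date could be the first stop or the last dose after restart. The protocol does not say.

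**6. Scale.** One patient in 40 is 1/40 = 2.5 percentage points. With assumed counts and exact intervals:

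| Responders | ORR | 95% CI | 85% CI |
|---|---|---|---|
| 4/40 | 10.0% | 2.8 to 23.7 | 4.0 to 20.0 |
| 5/40 | 12.5% | 4.2 to 26.8 | 5.7 to 23.0 |
| 6/40 | 15.0% | 5.7 to 29.8 | 7.5 to 26.0 |

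**The case against.** The best defence is that other text points to a stop at progression. Section 8.3 says lesions are followed until progression and calls what follows a quick reference to the full criteria. Sections 6.1.5 and 7.3 put patients off study at progression. ORR is secondary and descriptive, and detailed response derivations are often left to a statistical analysis plan. This limits the weight of the point but does not remove it. None of those passages defines the best-response window, they stand beside explicit permission to treat past progression, and section 8.3.2 does fix a window of its own.

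Several stronger readings are tempting and are not supported:
- A reader might infer that any patient with new lesions and later shrinkage becomes a responder. Table 2 blocks this while the new lesion persists, and section 8.2 itself describes the new-lesion picture at first evaluation as rare.
- A reader might infer that responses confirmed after stopping are lost. No sentence requires the confirming scan to be on treatment, so this is one reading and not a stated rule.
- A reader might object that the window opens at atezolizumab while progression-free time runs from carboplatin. The only CT in between is the one before cycle 1. A response seen there would still need confirmation at least 6 weeks later, inside the window, and section 8.1 already fixes screening as the reference. The effect on ORR is close to nil.
- A reader might take the approximately 10% in section 8.2 as the share of patients affected, which would be 4 of 40, or 10 points. That figure concerns benefit underestimated by conventional criteria in melanoma. It is not a rate of confirmed response after progression in this population.

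**Conclusion.** The point holds in a limited form. Section 8.3.2 bounds RECIST 1.1 best response by treatment, and no rule in the protocol removes responses that follow RECIST 1.1 progression. Such a response can count when progression came from target growth, or from a new lesion that later resolved, and the later fall of at least 30% below baseline was confirmed. The same window excludes responses first seen off treatment and leaves off-treatment confirmation undecided, although section 7.2.6 requires the scans.

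The size is 2.5 points of ORR per reclassified patient, assuming all 40 planned patients form the denominator. The number of such patients, and hence the net direction of any bias, cannot be derived from the protocol. The primary endpoint, the stage 1 rule and the final decision rule are unaffected.

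**What to change.** In section 8.3.2, define RECIST 1.1 best response as the best confirmed response, with the screening CT as reference, up to the first RECIST 1.1 progression or the start of subsequent anticancer therapy, whichever comes first, whether or not study treatment is still being given. State that scans taken off treatment under sections 7.2.6 and 7.4 count both for a first response and for confirmation. Report responses after RECIST 1.1 progression separately under iRECIST.

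The cost is one or two sentences and the matching derivation. No scan and no treatment rule changes. The start date of any later anticancer therapy must also be recorded for patients who stop without progression, since section 7.3 describes that collection under follow-up after progression. The one small downside is that post-progression responses no longer count in the headline ORR.

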**Table 2. Integration of target, non-target and new lesions into response assessment**

| Target Lesions                                                                 | Non-Target Lesions        | New Lesions | Overall Response | Best Response for this category also requires       |
|--------------------------------------------------------------------------------|---------------------------|-------------|------------------|-----------------------------------------------------|
| Patients with Target lesions <math>\pm</math> non target lesions |                           |             |                  |                                                     |
| CR                                                                             | CR                        | No          | CR               | Normalization of tumor markers, tumor nodes < 10 mm |
| CR                                                                             | Non-CR/Non-PD             | No          | PR               |                                                     |
| CR                                                                             | Not all evaluated         | No          | PR               |                                                     |
| PR                                                                             | Non-PD/ not all evaluated | No          | PR               |                                                     |

|                                                                                                                                                                                                                                                                                                                                                                                                                                                                       |                           |     |               |                                                         |
|-----------------------------------------------------------------------------------------------------------------------------------------------------------------------------------------------------------------------------------------------------------------------------------------------------------------------------------------------------------------------------------------------------------------------------------------------------------------------|---------------------------|-----|---------------|---------------------------------------------------------|
| SD                                                                                                                                                                                                                                                                                                                                                                                                                                                                    | Non-PD/ not all evaluated | No  | SD            | documented at least once $\geq 8$                       |
| Not all evaluated                                                                                                                                                                                                                                                                                                                                                                                                                                                     | Non-PD                    | No  | NE            |                                                         |
| PD                                                                                                                                                                                                                                                                                                                                                                                                                                                                    | Any                       | Any | PD            |                                                         |
| Any                                                                                                                                                                                                                                                                                                                                                                                                                                                                   | PD                        | Any | PD            |                                                         |
| Any                                                                                                                                                                                                                                                                                                                                                                                                                                                                   | Any                       | Yes | PD            |                                                         |
| Patients with Non target lesions ONLY                                                                                                                                                                                                                                                                                                                                                                                                                   |                           |     |               |                                                         |
| No Target                                                                                                                                                                                                                                                                                                                                                                                                                                                             | CR                        | No  | CR            | Normalization of tumor markers, all tumor nodes < 10 mm |
| No Target                                                                                                                                                                                                                                                                                                                                                                                                                                                             | Non-CR/non-PD             | No  | Non-CR/non-PD |                                                         |
| No Target                                                                                                                                                                                                                                                                                                                                                                                                                                                             | Not all evaluated         | No  | NE            |                                                         |
| No Target                                                                                                                                                                                                                                                                                                                                                                                                                                                             | Unequivocal PD            | Any | PD            |                                                         |
| No Target                                                                                                                                                                                                                                                                                                                                                                                                                                                             | Any                       | Yes | PD            |                                                         |
| 
Note: Patients with a global deterioration of health status requiring discontinuation of treatment without objective evidence of disease progression [or evidence of unequivocal disease progression] at that time should be reported as “symptomatic deterioration”. This is a reason for stopping therapy, but is NOT objective PD. Every effort should be made to document the objective progression even after discontinuation of treatment.
 |                           |     |               |                                                         |

Complete or partial responses may be claimed only if the criteria for each are met at a subsequent time point **at least 6 weeks later**. The best overall response can be interpreted as below:

